**Fig. 1 Fig1:**
[figure not shown]
Implementation strategy

**Table 1 Tab1:** Spirit time line

	Enrollment and Allocation					Post Allocation				Endline evaluation		Close Out	
**TIME POINTS**	-t4	-t3	-t2	-t1	t0	t1	t2	t3	t4	t5	t6	t7	t8
Team building	X	X											
Stake holder consultations and ethical proceedings	X	X											
Development of BCC Material			X	X									
Evaluation of BCC			X	X									
Preparation of questionnaire for baseline evaluation			X	X									
Baseline survey of knowledge of antenatal mothers					X								
Recruitment					X	X	X	X	X				
Training to antenatal women in intervention group (2 sessions)						X	X	X	X	X	X		
3rd training session – In postnatal period to intervention group								X	X	X	X		
Evaluation of training						X	X	X	X	X	X		
Interview with control mothers								X	X	X	X		
Endline evaluation of intervention								X	X	X	X		
Data analysis												X	X
Report writing												X	X

##### Sample size & sampling methodology

Anticipating a 5% exposure rate to neuro parenting among multigravida women during the study period and aiming for an odds ratio (OR) of 2 with 80% power and 95% confidence interval (CI), with 20% drop out rate the sample size calculation involves recruiting 513 participants per group, rounded to the nearest number, resulting in a total of 520 participants in each arm.

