## Background

Early childhood is a critical period for a child’s development. Developmental delays, if undetected and untreated, can have significant long-term consequences [1]. Developmental Delay (DD) pose a significant global health challenge, particularly affecting children in developing countries [2]. In South Asia, a staggering 53 million children under five are diagnosed with DD, with India bearing the brunt of this burden [3–5]. Globally, an estimated 180–200 million children under five experience developmental delays [6]. In India alone, at least 10% of young children are affected [7]. 

Preterm birth is one of the major contributors to neurodevelopmental disorders (NDDs) globally and in India. Studies indicate that one in two surviving preterm infants develops NDDs by the age of two. India contributes significantly to the global burden of preterm births, accounting for 23.4% of the total [8–11]. Premature infants often suffer from neurological impairments, such as incomplete myelination and immature brain development, which can lead to long-term developmental delays affecting their motor and cognitive abilities [12, 13]. Compounding this issue, factors like poverty, malnutrition, and limited access to healthcare further elevate the risk of DD [14]. Beyond the individual influence, DD have far-reaching consequences which impact multiple Sustainable Development Goals, including poverty, hunger, health, education, economic growth, and inequality [15]. Families of children with DD often face significant economic burdens, with 10% of mothers are forced to quit their jobs to care for their children [16]. In addition, socioeconomic factors such as poverty, malnutrition, and limited access to healthcare exacerbate the risk of DD [17].

Early identification of these delays is crucial for timely intervention and optimal outcomes [18, 19]. Parental awareness plays a key role in early detection, as parents are often the first to notice developmental deviations in their children [20]. However, a significant gap in maternal knowledge and awareness about developmental milestones and red flags persists, especially in rural and underserved regions in India, where access to healthcare resources is limited [21]. This lack of awareness will hinder the early identification and delay necessary interventions [22].

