#### Implementation phase

This Phase of the study employs a non-randomized intervention design to assess the impact of a targeted multimethod parental educational intervention on antenatal mothers. This phase seeks to provide valuable insights into the practical application and potential benefits of the neuro parenting program. A comparison is made between the intervention group, exposed to the neuro parenting program, and a control group receiving routine care without training sessions. The primary outcomes center around evaluating the percentage of mothers who suspect early childhood developmental disorders including true positive, false positive and false negative ratio. The confirmation of DD will be done using Bayley Scale for Infant Development IV. The study entails a meticulously structured follow-up period, with strategically defined time points to assess the program’s efficacy across critical stages of early development. Assessments will be conducted at birth, six months, and twelve months postpartum to monitor developmental trajectories. By demarcating these specific follow-up intervals, the study ensures a systematic framework for evaluating intervention outcomes, particularly the capacity of mothers to recognize neurodevelopmental indicators and suspect potential developmental disorders. This follow-up design is structured to capture the program’s lasting influence on maternal awareness and accuracy in identifying developmental milestones, offering a precise evaluation of the intervention’s long-term impact. Through targeted assessments, the study will measure both immediate and long-term effects on maternal ability to recognize early developmental cues, providing a focused understanding of the intervention’s effectiveness. Implementation strategies are illustrated in Fig. 1 and the timeline has been depicted in Table 1.

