### Training and assessment

In this phase, all participants will undergo a thorough assessment of training outcomes. The implementation strategy involves providing participants with a comprehensive questionnaire covering knowledge, awareness, and practices related to identifying early child development delays based on the training module. This questionnaire will be administered after the completion of the training module. Upon concluding all training sessions, a final questionnaire will be developed to gauge participants’ overall knowledge, practice, and understanding of the training’s importance. Descriptive statistics will be calculated to analyse quantitative variables, providing insights into the numerical aspects of the participants’ responses. For quantitative variables, frequencies and percentages will be computed, offering a quantitative overview of the participants’ understanding and practices. To explore the association between variables, the chi-square test will be employed, with a significance level set at 5%.

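### The stated 80% power rests on an exposure rate among multigravida women, not on a control-group rate of the primary outcome, so it does not apply to that outcome

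*Protocol article*

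**What the plan says.** All references are to the protocol article.

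- **Sample size & sampling methodology.** The base rate is given as "Anticipating a 5% exposure rate to neuro parenting among multigravida women during the study period". The effect is an odds ratio of 2, at 80% power and 95% confidence. The text continues "with 20% drop out rate the sample size calculation involves recruiting 513 participants per group", and after rounding, "resulting in a total of 520 participants in each arm".
- **Implementation phase.** The primary outcome is set differently: "The primary outcomes center around evaluating the percentage of mothers who suspect early childhood developmental disorders". The same sentence adds the true positive, false positive and false negative ratio, and DD is to be confirmed with the Bayley scale. The comparison is between a group given the programme and a group under routine care.
- **Methodology and Eligibility criteria.** Participants are antenatal mothers from the second trimester. Neither section restricts entry by gravidity.
- **Training and assessment.** The test named is chi-square at the 5% level.
- **Background.** The only general frequency of DD among young children in India is "In India alone, at least 10% of young children are affected".

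**The concern.** A power statement for a two-group comparison needs the outcome proportion expected under control and the difference to be detected. The 5% here is neither. It describes how many women would meet neuro-parenting, and in this study that is fixed by group. It also refers to multigravida women, who are only part of the eligible population. No proportion of mothers expected to suspect a disorder, rightly or wrongly, enters the calculation.

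The 80% therefore cannot be used to interpret the result. If the groups do not differ, a reader may take this as evidence against the programme from a study with 80% power, although that power was never worked out for the outcome. The risk is greatest for detection accuracy. True positives and false negatives can occur only in children who have DD, a minority of each arm, and the Interim and follow-up section says that true positives show whether the teaching works.

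**Working it through.** **Inputs from the article:** base rate 5%, odds ratio 2, power 80%, 5% significance level, dropout 20%, 520 per arm. A two-sided test is inferred from the 95% confidence level and the chi-square test. Evaluable per arm: 520 × 0.80 = 416.

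**Inputs that are assumptions:** the control proportion of mothers who suspect a disorder, control sensitivity, and DD prevalence in this cohort (10% borrowed from the Background).

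**1. Reproducing the plan's figure.** An odds ratio of 2 from p₁ = 0.05 gives p₂ = (2 × 0.05)/(0.95 + 2 × 0.05) = 0.0952. With unpooled variance:

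n = (1.960 + 0.842)² × [0.05 × 0.95 + 0.0952 × 0.9048] / (0.0952 − 0.05)² = 7.849 × 0.13367 / 0.0020465 = 512.7, so 513.

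This matches the printed 513 exactly, with no dropout allowance in it. The arithmetic is an ordinary comparison of two proportions; the difficulty lies in what the 5% stands for.

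**2. Power for the share of mothers who suspect a disorder.** With p̄ the mean of p₁ and p₂:

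power = Φ{ [√n (p₂ − p₁) − 1.96 √(2p̄(1 − p̄))] / √(p₁(1 − p₁) + p₂(1 − p₂)) }

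Example, n = 416, p₁ = 0.05: (20.396 × 0.04524 − 1.96 × 0.3670) / 0.3656 = 0.556, and Φ(0.556) = 0.71.

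| Assumed control rate | Rate at odds ratio 2 | Power, 416 per arm | Power, 520 per arm |
|---|---|---|---|
| 1% | 2.0% | 21% | 26% |
| 2% | 3.9% | 37% | 45% |
| 5% | 9.5% | 71% | 80% |
| 8% | 14.8% | 87% | 93% |
| 10% | 18.2% | 93% | 97% |
| 20% | 33.3% | 99% | above 99% |

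Power reaches 80% at a control rate of about 6.3% with 416 per arm, and about 5.0% with 520.

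**3. Power for sensitivity.** Expected children with DD per arm at 10% prevalence: 0.10 × 416 = 41.6. The same formula with n = 41.6 and odds ratio 2 on sensitivity gives:

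| Assumed control sensitivity | Sensitivity at odds ratio 2 | Power |
|---|---|---|
| 20% | 33.3% | 28% |
| 30% | 46.2% | 33% |
| 40% | 57.1% | 34% |
| 50% | 66.7% | 34% |

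Over the same control sensitivities, power is 16-19% at 5% prevalence (20.8 children per arm) and 39-48% at 15% (62.4 per arm).

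**4. Precision for sensitivity.** The 95% confidence interval for the difference is widest when both sensitivities are 0.5. The half-width is then 1.96 × √(2 × 0.25/41.6) = 0.215, or about 21 points.

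**The case against.** **Power may be adequate.** A reader might infer that because the input is wrong, power for the primary outcome must be far below 80%. The article does not support this. A mislabelled base rate does not fix the direction of the error. The first-named outcome counts all mothers, and the same formula serves two outcome proportions. If 5% happened to be the control rate of suspicion, the calculation would fit the comparison, apart from the dropout allowance, which is a separate matter. At a control rate of 10%, power exceeds 90%. This objection stands: for that outcome, power is undetermined.

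**Low power for sensitivity rests on borrowed figures.** This is also true. The article gives no control sensitivity, and its 10% is a national background figure, stated as a minimum, not a forecast of Bayley-confirmed DD in this cohort. The results in steps 3 and 4 are conditional and are shown over a range for that reason. False positives arise in children without DD, so the small denominator does not describe the whole primary outcome.

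**Prevalence could be much higher.** The Background reports NDDs in one in two surviving preterm infants by age two, and the Intervention section mentions mothers of preterm babies. But mothers enter from the second trimester, before preterm birth is known, so that rate cannot be applied to the whole cohort.

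**Yield per mother.** A reader might restate sensitivity as confirmed true positives per mother and report very low power. Going from 40% to 57.1% sensitivity at 10% prevalence means 4.0% versus 5.7% of mothers, an odds ratio of (0.057/0.943)/(0.040/0.960), about 1.45. That is a smaller effect than the article's odds ratio of 2, so its power cannot be set beside the figures above. At odds ratio 2 from 4.0% (to 7.7%), power with 416 per arm is 62%.

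**An article condenses.** Details may sit in the full protocol. But this article does print a calculation, and the quantity it names is not the outcome, so this is not a detail left out.

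**Conclusion.** The point holds in a limited form. The 5% is neither a control-group rate of the primary outcome nor a rate in the eligible population, and the stated 80% power does not apply to the primary outcome. This rests on the article's wording alone.

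The size of the consequence depends on the component:

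- **Share of mothers who suspect a disorder:** power at odds ratio 2 may lie below or above 80%. The article does not give the control rate that would decide it.
- **True positives and false negatives:** power for odds ratio 2 is low, about 28-34%, if prevalence is near 10% and control sensitivity is 20-50%. It stays below 50% at 15% prevalence. Both inputs are assumptions.

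A general claim that the study is badly underpowered for its primary outcome would go beyond the document.

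**What to change.** In the sample size section:

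1. Remove the exposure rate and the reference to multigravida women. State the control proportion and the effect expected for the primary outcome, with the source of each.
2. State the power that 520 enrolled and 416 evaluable per arm give for that outcome. If the control proportion is uncertain, give power over a range of control rates, as in the first table above.
3. Present detection accuracy as estimation. State the expected number of children with DD per arm and the expected confidence-interval half-width for the difference in sensitivity. On the assumptions used here these are about 42 children and about 21 points at most. Label both as assumption-based, and replace them if the team has better figures.

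Cost: some work to find and justify a control proportion, then a change of text. No extra participants are needed. The downside is that the stated power may become less favourable than 80%.

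### The 513 per group is the size before dropout: 520 per arm with the planned 20% loss gives about 71% power for an odds ratio of 2, not 80%

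*Protocol article*

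**What the plan says.** The whole calculation is one sentence in the protocol article, under *Sample size & sampling methodology*. It starts from a base rate ("Anticipating a 5% exposure rate to neuro parenting among multigravida women during the study period"), sets the target as "aiming for an odds ratio (OR) of 2 with 80% power and 95% confidence interval (CI"), and continues "with 20% drop out rate the sample size calculation involves recruiting 513 participants per group". That number is then rounded, "resulting in a total of 520 participants in each arm".

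The type I error is not given in that sentence beyond the 95% confidence level. The section *Training and assessment* supplies it: "the chi-square test will be employed, with a significance level set at 5"%.

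Dropout is listed with the other inputs, and 513 is described as the number to recruit. As written, both 513 and 520 therefore already allow for 20% loss.

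**The concern.** A calculation that allows for 20% dropout should recruit one quarter more than it needs to analyse, since 1/0.8 = 1.25. A recruitment figure of 513 would then imply about 410 evaluable women per arm. For a rise from 5% to the proportion implied by an odds ratio of 2, at two-sided 5%, 410 looks too few for 80% power, while 513 looks like the evaluable requirement itself.

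If the allowance is missing, the stated power is true only when almost nobody is lost. That is unlikely here: women are enrolled from the second trimester, the last assessment is twelve months after birth, and the plan itself expects 20% to drop out. The funder, the ethics committee and readers would be relying on a chance of detecting the target effect that the design does not offer on its own assumptions.

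**Working it through.** **Inputs**

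- Reference proportion p1 = 0.05 (sample size section). The article calls this an exposure rate; using it as the comparison-group proportion is an assumption.
- Odds ratio 2 and 80% power (sample size section); z = 0.8416.
- Two-sided 5% (95% confidence level in the sample size section, 5% chi-square test in *Training and assessment*); z = 1.96.
- Dropout 20%, equal arms, 520 per arm (sample size section).

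**Step 1: second proportion.** p2 = 2 × 0.05 / (0.95 + 2 × 0.05) = 0.10/1.05 = 0.0952. The difference is 0.0452.

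**Step 2: reproduce the plan's figure.** Unpooled two-proportion formula:

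n = (1.96 + 0.8416)² × [p1(1 − p1) + p2(1 − p2)] / (p2 − p1)²
= 7.849 × (0.0475 + 0.0862) / 0.002046
= 512.7, so **513 per group with no dropout**.

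The pooled formula, which corresponds to the chi-square test, gives 515.4, so 516. With continuity correction it is 559.

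**Step 3: add the 20% dropout.**

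| Base size | ÷ 0.8 | × 1.2 (too small, but often used) |
|---|---|---|
| Unpooled, 513 (512.66 unrounded) | 642 (641 from unrounded) | 616 |
| Pooled, 516 | 645 | 620 |

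None of these is 513 or 520.

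**Step 4: look for a reading under which 513 does include dropout.**

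- One-sided 5%, divided by 0.8: 505 (unpooled) to 508 (pooled). Close, but not 513, and at odds with the 95% confidence level.
- The 2 read as a risk ratio (5% against 10%), multiplied by 1.2: 518 (unpooled) to 522 (pooled). Not 513, and at odds with the stated odds ratio.
- The same risk ratio, divided by 0.8: 540 to 544.

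Only the two-sided calculation without dropout returns 513 while using the other inputs as stated.

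**Step 5: power of the design as planned.** The rounding covers (520 − 513)/520 = 1.3% loss. With 20% loss, 520 × 0.8 = 416 per arm remain.

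Pooled power at 416: the standard error is 0.01799 under the null and 0.01793 under the alternative, so z = (0.04524 − 1.96 × 0.01799)/0.01793 = 0.556 and power = 0.711.

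| Analysed per arm | Power, pooled | Power, unpooled |
|---|---|---|
| 520 (no loss) | 80.3% | 80.6% |
| 416 (20% loss from 520) | 71.1% | 71.4% |
| 410 (20% loss from 513) | 70.5% | 70.7% |

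With continuity correction, power at 416 is 66.4%.

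**Step 6: detectable effect.** Solving for the odds ratio that gives 80% power at 416 per arm with p1 = 0.05 gives 2.14 (both formulas agree to two decimals).

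**The case against.** The strongest objection concerns the 5%. The article describes it as exposure to neuro-parenting among multigravida women. That is not the proportion of control mothers who suspect a disorder, which is what the primary outcome measures. Exposure is fixed by arm in this study, so the true power depends on a control outcome rate that the article does not give. For assumed control rates of 3%, 5%, 8% and 10%, power at 416 per arm and odds ratio 2 is about 51%, 71%, 87% and 93% (pooled formula). This stands as a limit: 71% is the power on the plan's own inputs and not a forecast for the real comparison. It does not rescue the stated 80%, which rests on the same 5%. Nor does it change the finding about 513, because the two-proportion arithmetic is the same whether the 5% is an exposure or an outcome proportion.

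Three smaller points are fair:

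- The article names no formula or software, so the omission of the dropout step is inferred from the exact match at 513.
- The corrected target depends on the formula: 642 unpooled, 645 pooled.
- The figure of 416 assumes that a woman who drops out contributes nothing to the primary outcome. With assessments at birth, six and twelve months, some might contribute. If all 520 were analysed, power would be 80.3%. But an allowance for dropout in a sample size only makes sense if those women are lost to the analysis.

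**Conclusion.** The concern holds. The article's 513 per group is the size needed with complete data, and the 20% dropout it claims to include is not in it. Taking the plan's 5% as the reference proportion, a two-sided 5% test and 20% loss in each arm, 520 enrolled per arm gives about 71% power for an odds ratio of 2. The type II error is then about 29%, where the plan implies 20%. The shortfall against the size required after dropout is 122 per arm (642 − 520), or 125 with the pooled formula (645 − 520).

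The error biases no estimate and does not affect the type I error. It does make a stated property of the design wrong on the document's own figures, and a separate analysis plan could not change that.

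**What to change.** Rewrite the sample size sentence and delete the claim that 513 already includes dropout. There are two ways to do it:

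1. **Keep 520 per arm.** State that 513 per group is the evaluable number for 80% power, that 520 enrolled with 20% loss leaves 416, and that power for an odds ratio of 2 is then about 71% (80% power for an odds ratio of about 2.14). This costs only a wording change and a less favourable power statement.
2. **Keep the 80% claim.** Raise enrolment to about 642 per arm (645 with the pooled formula), which adds 122 to 125 women per arm, or 244 to 250 in total.

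Either way, name the formula used and say what the 5% represents. If it is not the expected proportion in the control group for the primary outcome, recompute the size and the power from that proportion before restating them.

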##### Intervention

Antenatal women with willingness to participate will be enrolled in the study after obtaining Informed Consent. The antenatal mothers who visit the hospital for antenatal care will be explained about the online module regarding its uses and accessibility of the information. In addition, they will be provided information regarding observing the growth and activities of the child. For the control group, antenatal mothers enrolled as controls, regular check ups as per the standard protocol and the printed material for identification of neurodevelopmental signs will be provided. The intervention comprises three strategically timed training sessions during the second trimester, third trimester and postnatal care, specifically targeting mothers of preterm babies.

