### Methodology

This non randomized interventional study will be carried out among Antenatal mothers from 2nd Trimester of pregnancy at SRM Medical College Hospital, Research Centre, other established centres in Chennai and Trichy and Tanjavur Medical College, Tanjavur, Tamil Nadu, India. The study was approved by the Institutional Ethical Committee with the reference number 8688/IEC/2023 and was accepted by Indian Council of Medical Research (ICMR), a peer reviewed funding agency after reviewing for the methodological soundness. (Proposal id IIRP-2023-7817/F1). Trial has been registered under Clinical Trials Registry (CTRI/2024/04/065008).

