### Eligibility criteria

For the intervention group, eligible participants include antenatal mothers who have provided informed consent and are willing to participate in the neuro-parenting program. These participants will need to be available for follow-up assessments at specified intervals to evaluate the intervention’s impact on early childhood development awareness. The control group will comprise antenatal mothers who are receiving routine antenatal and postnatal care without access to the neuro-parenting intervention; they will also provide informed consent and commit to follow-up visits. Exclusion criteria for both groups will include any mothers with medical conditions that could independently influence neurodevelopmental outcomes, as well as those who may face challenges in completing the follow-up.

**The study will be conducted in three phases namely**,

Preparatory Phase.Implementation Phase.Evaluation Phase.

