#### Evaluation phase

This phase will assess the effectiveness of training program and the incidence of the DD among children born to mothers who participated in the training program. Mothers will have to undergo at least 2 of the three educational/training sessions.

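### The sessions are said to target mothers of preterm babies, a target that eligibility, Table 1 and the control arm do not share; followed as written, it can enrich the trained group for delay

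*Protocol article*

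**What the plan says.** All references are to the protocol article.

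- **Methodology:** "This non randomized interventional study will be carried out among Antenatal mothers from 2nd Trimester of pregnancy".
- **Eligibility criteria:** for the intervention group, "eligible participants include antenatal mothers who have provided informed consent and are willing to participate in the neuro-parenting program". For controls, "The control group will comprise antenatal mothers who are receiving routine antenatal and postnatal care without access to the neuro-parenting intervention". Both groups exclude "any mothers with medical conditions that could independently influence neurodevelopmental outcomes". No criterion concerns prematurity or gestational age at birth.
- **Intervention:** three sessions, in the second trimester, the third trimester and postnatally, "specifically targeting mothers of preterm babies".
- **Table 1:** two sessions go to antenatal women in the intervention group and the third, postnatal, session to the intervention group. Neither row carries a preterm limit.
- **Evaluation phase:** "Mothers will have to undergo at least 2 of the three educational/training sessions". Controls receive no sessions, so they can have no matching requirement. The Survey on neurodevelopmental outcomes is likewise directed at mothers who attended.
- **Implementation phase:** the primary outcomes are the percentage of mothers who suspect a disorder and the true-positive, false-positive and false-negative ratios, with delay confirmed on the Bayley scale.
- **Interim and follow-up:** true positives are taken as the evidence that the teaching works.
- **Training and assessment:** the only test named is a chi-square at 5%.
- **Background:** "one in two surviving preterm infants develops NDDs by the age of two", against at least 10% of young children in India affected by delay.

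**The concern.** The article describes two populations for one programme. At second-trimester enrolment nobody can yet be known as the mother of a preterm baby, so the target in the Intervention section cannot be the population that Eligibility criteria recruits. The target is stated only for the trained group.

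Allocation is not randomised, so nothing in the design balances preterm birth between the arms, and the Background itself presents it as a strong risk factor for delay. The percentage of mothers who suspect a disorder and the number of true positives both rise with the prevalence of delay among the infants, whatever the mother has learned. A trained group with more preterm births would therefore score higher on both with no training effect, and an unadjusted chi-square cannot separate case mix from training.

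**Working it through.** No figure in the plan is disputed here. The check asks which readings of the Intervention section create an imbalance, and how large it could be.

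**Readings**

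| Reading of the target | Consequence for comparability |
|---|---|
| A matter of content or emphasis only; all intervention mothers are offered all three sessions, as in Table 1 | No imbalance from this source |
| Recruitment leans towards women at risk of preterm birth | More preterm births in the trained arm; the documents give no basis for the amount |
| Postnatal session for mothers of preterm babies only, and at least two sessions required to be evaluated | Mothers of preterm babies have three chances to qualify, mothers of term babies two |

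**Size under the third reading**

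From the Background: delay in 50% of preterm infants. Assumed, because the documents do not give them: preterm share p of 10 to 15%; attendance a of 60 to 80% per session, independent and equal in both groups of mothers; delay in t = 5 to 10% of term infants; mothers' sensitivity 0.5 and false-positive rate 0.05 in both arms, so that training does nothing.

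- Term mothers qualify with probability a².
- Preterm mothers qualify with probability a³ + 3a²(1−a).
- Preterm share among qualifiers: s = p·P(preterm qualifies) / [p·P(preterm qualifies) + (1−p)·P(term qualifies)].
- Delay prevalence: D = 0.5s + t(1−s) in the trained set, and 0.5p + t(1−p) in controls.
- Proportion suspecting: 0.5D + 0.05(1−D) = 0.05 + 0.45D.
- True-positive yield: 0.5D.

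Worked example with p = 13%, a = 0.7, t = 10%:

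- Qualifying: 0.49 for term; 0.343 + 0.441 = 0.784 for preterm.
- s = 0.1019 / (0.1019 + 0.4263) = 19.3%, against 13% in controls.
- D = 17.7% against 15.2%, a gap of 2.5 points.
- Suspicion 13.0% against 11.8%, odds ratio 1.11.
- True-positive yield 8.9% against 7.6%, odds ratio 1.18.

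Ends of the range:

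| p, a, t | Preterm share, trained | Delay, trained v control | Gap (points) | OR, suspicion | OR, true-positive yield |
|---|---|---|---|---|---|
| 10%, 0.8, 10% | 13.5% | 15.4% v 14.0% | 1.4 | 1.06 | 1.11 |
| 15%, 0.6, 5% | 24.1% | 15.85% v 11.75% | 4.1 | 1.20 | 1.38 |

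**Effect of early delivery**

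A mother who delivers before the third-trimester session is left with two sessions and qualifies with probability a², as a term mother does. If half of the preterm mothers miss that session, the gap falls to about 0.7 to 2.2 points. If all do, it is zero.

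**What is not affected**

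Sensitivity is true positives divided by true positives plus false negatives. In this set-up it is 0.5 in both arms at any prevalence.

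**The case against.** The strongest reply is that this is one loose clause. Table 1 offers the postnatal session to the whole intervention group and Eligibility criteria sets no preterm limit, so the target may describe emphasis only. The Evaluation phase does not say that mothers with fewer than two sessions leave the comparison, and Training and assessment speaks of assessing all participants. Adjustment and analysis sets may also be specified in a fuller document that is not shown.

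Much of this stands. The imbalance is not built in under every reading, and the absence of a covariate list from an article is not itself a fault. But the article does state incompatible targets, nothing in it says which governs, and following the Intervention and Evaluation sections as written can create the bias.

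Two stronger inferences are tempting and should not be drawn.

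- **A prevalence odds ratio of 9.** A reader might set the Background's 50% in preterm infants against 10% in young children: (0.5/0.5) / (0.1/0.9) = 9. That needs a wholly preterm trained arm, which second-trimester enrolment cannot produce. The 50% also refers to age two, while follow-up ends at twelve months; the same caution applies to its use in the working above.
- **A bias nearly as large as the planned effect.** A reader might set the 1.4 to 4.1 points beside the 4.5 points implied by the sample size (5% with an odds ratio of 2 gives 9.5%). The former are points of delay prevalence; the plan's 5% is an exposure rate to neuro-parenting. The two are not comparable, and the shift in suspicion is diluted by mothers' detection to about 0.6 to 1.8 points (0.45 times the prevalence gap).

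**Conclusion.** The concern holds as a conflict over the target population that can bias two of the reported outcomes; it does not show that the comparison must be biased. The Intervention section disagrees with Methodology, Eligibility criteria and Table 1, and its target has no counterpart among controls.

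If it guides recruitment, or limits the postnatal session while the attendance rule is used as a filter, the percentage suspecting and the true-positive yield can be raised without any training effect. By the filter route the inflation is modest: odds ratios of about 1.06 to 1.20 and 1.11 to 1.38 respectively, falling towards 1 as early delivery removes the third-trimester session. These figures depend on the assumed preterm share, attendance, term risk, sensitivity and false-positive rate. For the recruitment route the documents support no figure. Sensitivity among delayed infants is not biased by prevalence alone.

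This should be fixed; it is not a fatal flaw.

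**What to change.** 1. Reconcile Methodology, Eligibility criteria, Table 1, Intervention and Evaluation phase on who the programme is for. Who receives which session is for the sponsor to settle.
2. Apply one population definition to both arms.
3. Make the primary comparison among all enrolled mothers in both arms, regardless of sessions attended or gestational age at birth. An analysis limited to mothers with at least two sessions can be kept as a supporting one.
4. Record gestational age at birth in both arms, and adjust or stratify the primary comparison for preterm birth instead of relying on the unadjusted chi-square alone.

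The cost is wording in the affected sections, one extra recorded variable and one covariate. The variable should be in place before follow-up data are collected.
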